**Fig 1: Study enrolment, randomisation and evaluation plan**

**PHASE I STUDY**

**1,650 school-aged children will provide stool samples**

**Questionnaire survey will be done together**

**PHASE II STUDY**

**212 positive cases of hookworms assuming prevalence of hookworm is 12%**

**212 positive cases of hookworms will provide stool samples**

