**Faecal egg counts from hookworm positive**

**stool samples**

**Albendazole**

**Dual-dose treatment with avocado (n=53)**

**Albendazole**

**Dual-dose without avocado treatment (n=53)**

**Albendazole**

**Single-dose treatment with avocado**

**(n=53)**

**Albendazole**

**Single-dose treatment without avocado (n=53)**

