**21 days later after treatment**

**(5% follow up loss)**

**Cure rate and egg reduction rate will evaluated**

## 3.3 Sampling method for prevalence survey

**3.3.1 Selection of schools**

Of 504 schools in Mayuge district, 33 schools will be selected randomly and independently from the school list stratified by the parish and sub-county using probability proportional to size selection (PPS). Before the sample selection, the sampling frame will be sorted within each sampling stratum first, by size. The required number of schools shall then be selected by probability proportional to size (PPS).

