**For phase II:**

For the trial phase of the study, the aim is to assess the effect of co-administration with fatty foods, and of dual-dose versus single-dose albendazole on hookworm cure rate. The cure rate of single dose albendazole for hookworms varies between 36% and 93% in previously reported studies. Based on data from Adegnika et al (42), we power our trial to detect a difference in cure rate of 70% versus 50% for both co-administration with fatty foods versus no co-administration, and for dual-dose versus single-dose albendazole.

With type I error probability of 5%, 93 participants in each comparison group will be required for 80% power to detect a difference in cure rate of 70% versus 50%. Therefore, the total target sample size for the trial will be 186. However, allowing for 5% loss to follow-up, i.e. 5% of hookworm positive cases not appearing on the follow up stool test 21 days after treatment, the target sample size will increase to 196. If the expecting prevalence of hookworm in 2021 is 12%, to satisfy the sample size of 196, the target sample size of the prevalence survey of 2021 will be 1,634. Therefore, a total sample size of 1,650 will be sufficient to cover sample size requirements of both the prevalence survey and the nested trial.

Assuming that 50 children will be selected from each school, a total of 33 schools will be randomly selected in order to achieve the required sample size.

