**The scenario of not having enough number of participants for the phase II trial:**

If the prevalence of hookworm in the survey is lower than anticipated so that the target sample size of 196 for the phase II trial is not achieved, the MANE team will purposely select hookworm high prevalence school(s) and test for hookworm among those who are not taking part in the phase I prevalence survey. For example, after the phase I prevalence survey, if twenty more participants will be needed, and the prevalence of hookworm in school “A” is 50%, the MANE team will additionally select approximately 40 students in school “A”.

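### Fig 1's trial size of 212 (53 per arm) matches neither 12% of 1,650 (198) nor the target of 196 (49 per arm) derived in section 3.6

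*Protocol*

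**What the plan says.** Fig 1 in section 3.2 of the protocol sets out enrolment, randomisation and evaluation. It begins with "1,650 school-aged children will provide stool samples", then gives "212 positive cases of hookworms assuming prevalence of hookworm is 12" per cent, and repeats the number: "212 positive cases of hookworms will provide stool samples". All four arms carry the same size, for example "Dual-dose treatment with avocado (n=53") and "Single-dose treatment without avocado (n=53"). The last step allows "5% follow up loss".

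Section 3.6.1, phase II, powers each factorial comparison for cure rates of 70% versus 50%. It obtains 93 per comparison group and 186 in total, and after 5% loss says "the target sample size will increase to 196". It then divides by 12% prevalence to get 1,634 children and rounds up to 1,650. The contingency that follows applies when "the target sample size of 196 for the phase II trial is not achieved"; extra children are then tested in purposively chosen high-prevalence schools.

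**The concern.** The figure and the text share three inputs (1,650 children, 12% prevalence, 5% loss) but give two trial sizes, 212 and 196. The figure's number also fails on its own terms, because it is presented as the yield at 12% and 12% of 1,650 is smaller. Nothing in the protocol derives 212 or 53, or links them to 196.

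Fig 1 is the only place that prints a per-arm number, so readers would take the planned arm size from it. The yield expected on the protocol's own inputs lies between the two numbers. The most likely outcome of the survey would therefore satisfy section 3.6.1 and still look incomplete against Fig 1.

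**Working it through.** **Inputs.** Fig 1: 1,650 surveyed, 12% prevalence, 212 positives, 53 per arm, 5% loss. Section 3.6.1: 70% v 50%, type I error 5%, 80% power, 93 per group, 186, 196, 1,634 and 1,650. Sidedness is not stated, so two-sided is assumed.

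**1. Reproduce section 3.6.1.** The pooled normal formula without continuity correction, with mean proportion 0.60, is

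n = [1.960·√(2·0.60·0.40) + 0.842·√(0.50·0.50 + 0.70·0.30)]² / 0.20² = (1.358 + 0.571)² / 0.04 = 93.0, so 93 per comparison group.

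- Total: 2 × 93 = 186.
- After 5% loss: 186 / 0.95 = 195.8, so 196, or 196 / 4 = 49 per arm.
- Survey needed: 196 / 0.12 = 1,633.3, so 1,634.

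Every figure in the section agrees.

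**2. Test Fig 1.**

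- Yield: 1,650 × 0.12 = 198, not 212. The difference is 14 (14 / 198 = 7%).
- Arms: 4 × 53 = 212, so the figure agrees with itself and this is not a text-extraction fault.
- Against the derived target: 212 − 196 = 16 (16 / 196 = 8%), or 53 v 49 per arm.
- What 212 would need: 212 / 0.12 = 1,767 children, or a prevalence of 212 / 1,650 = 12.85%.

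**3. Look for another route to 212.**

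| Variant | Per group | Total | After 5% loss |
| --- | --- | --- | --- |
| Pooled, two-sided | 93 | 186 | 196 |
| With continuity correction | 103 | 206 | 217 |
| Unpooled variance | 91 | 182 | 182 / 0.95 = 191.6, so 192 |
| One-sided 5% | 74 | 148 | 148 / 0.95 = 155.8, so 156 |

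None gives 212. Rounding to whole blocks of 8 does not either (212 / 8 = 26.5). A loss of 12% would (186 / 0.88 = 211.4, so 212), but Fig 1 and section 3.6.1 both state 5%.

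**4. Effect on power per factorial comparison, 70% v 50%, after 5% loss.**

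- 196 randomised: 196 × 0.95 = 186 evaluable, power 80.0%.
- 212 randomised: 212 × 0.95 = 201 evaluable, power about 83%.

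**5. How likely the gap is to matter.** Treat the yield as binomial with 1,650 children and 12%, ignoring clustering by school and all exclusions. Then P(at least 196) = 0.571 and P(at least 212) = 0.153, so P(196 to 211) = 0.571 − 0.153 = 0.418. On that simple model, about two surveys in five would land between the two numbers.

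**The case against.** The strongest reply is that the operative text has one target. Section 3.6.1 sets 196, and the contingency is tied to 196 by name. Fig 1 is a flow diagram that states no trigger and no stopping rule. This stands, and it limits the point. A reader might infer that enrolment and the top-up run on two competing targets, so that field teams would act differently. The protocol does not support that: there is one written trigger, and no passage closes enrolment at 196 or at 212. Section 3.2 has hookworm-positive children from the survey go on to the trial, and the survey itself is fixed at 33 schools and about 1,650 children.

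A reader might also see a risk of bias because the trial is open-label. That does not follow either, since the top-up depends on how many children screen positive before any treatment.

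A third reply is that the gap is small: 14 children is about one binomial standard deviation of the yield (√(1,650 × 0.12 × 0.88) = 13.2). That is true of the realised count, but Fig 1 presents 212 as what 12% implies, so sampling variation does not explain it.

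Lastly, the document alone cannot show which number was intended, since a loss allowance near 12% would give 212. This also stands, and it is why the request is to reconcile the numbers. The derivation and the stated 5% do point to 196.

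**Conclusion.** The point holds as an inconsistency between the figure and the text. Fig 1's 212 positives and 53 per arm are wrong on the protocol's own inputs: the expected yield is 198, and the derived target is 196 (49 per arm, about 186 evaluable). The practical consequence is narrow. A yield of 196 to 211 meets section 3.6.1 and starts no top-up, but falls short of Fig 1. It would be wrong to read this as an underpowered trial, because either size gives at least 80% power per factorial comparison under the stated assumptions.

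The conclusion rests on a two-sided 5% test, which reproduces 93 exactly, and on the stated 12% prevalence and 5% loss. The mismatch between 212 and 12% of 1,650 needs only the protocol's own prevalence and survey size.

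**What to change.** State one trial size throughout. On the document's own inputs, change Fig 1 to about 198 expected hookworm positives before the section 3.2 exclusions, and a target of 196 randomised (49 per arm, about 186 evaluable after 5% loss). This corrects one figure and leaves the design, the power and the top-up rule as they are.

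The words *before exclusions* matter, because 198 leaves room for only two losses before 196. Section 3.2 excludes children with other parasites, and section 3.6.1 expects 18% schistosomiasis. The overlap with hookworm is not given. Assuming that schistosomiasis counts as another parasite, no overlap leaves 198 and independence leaves about 162 (198 × 0.82). A positive association would leave fewer. The corrected figure should therefore not present 198 as the number available for randomisation.

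If 212 is what the sponsor intends, derive it in section 3.6.1 with its loss allowance, change the 5% in both places if that is the source, raise the required survey size (about 1,767 at 12%, or 1,767 / 50 = 35.3, so 36 schools rather than 33), and reset the top-up trigger to 212. That option costs about 117 more children screened (1,767 − 1,650).

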**Faecal egg counts from hookworm positive**

**stool samples**

**Albendazole**

**Dual-dose treatment with avocado (n=53)**

**Albendazole**

**Dual-dose without avocado treatment (n=53)**

**Albendazole**

**Single-dose treatment with avocado**

**(n=53)**

**Albendazole**

**Single-dose treatment without avocado (n=53)**

**21 days later after treatment**

**(5% follow up loss)**

**Cure rate and egg reduction rate will evaluated**

## 3.3 Sampling method for prevalence survey

**3.3.1 Selection of schools**

Of 504 schools in Mayuge district, 33 schools will be selected randomly and independently from the school list stratified by the parish and sub-county using probability proportional to size selection (PPS). Before the sample selection, the sampling frame will be sorted within each sampling stratum first, by size. The required number of schools shall then be selected by probability proportional to size (PPS).

**3.3.2 Selection of classes**

Within each selected school, a class (40-50 children) will be selected among the P4 and P5 classes (9-10-year-old schoolchildren) using a table of random numbers or a lottery method. If only one class of this age group is present that class has to be selected. If the number of children present in the selected class is lower than 35, a second class will be selected and all children in both classes examined.

## 3.4 Randomisation into four groups for the trial

When positive hookworm cases are identified through the prevalence survey, field workers will notify the students of "positive" results. These students will be requested to visit the school where they attend for participating in the trial. The field researchers will be formed by health personnel from the most accessible health centre IV or hospital-level health facility in Mayuge district: 1) Mayuge health centre IV located in Mayuge town council, 2) Kigandalo health centre IV located in Kigandalo sub-county, 3) Kityerera health centre IV located in Kityerera sub-county, and 4) Buluuba hospital in baitambogwe sub-county. The participants will be instructed to have a meal on the morning of the visit, following the protocol for taking fatty meal with albendazole as outlined in the study of Nagy *et al.*(25). These participants will be randomised into one group among four treatment options by applying the block randomisation method, stratified by health facility. The randomisation block size will be 8, and within each block there will be two participants allocated to each of the four trial arms. A randomisation list will be prepared beforehand using a random number generator. Each health facility will have its own random number list. The participants will take a meal four hours after the drug consumption to exclude the possibility of affecting albendazole absorption by immediate taking foods. But, water, no caffeine drinks, non-alcoholic beverages can be allowed during four hours fasting period.

Albendazole (AGOZOLE 400mg; batch number T11098, produced by AGOG Pharmaceutical Ltd., India) will be used for this trial. This is not a new drug. AGOZOLE albendazole is approved by the National Drug Authority (NDA) of Uganda and is widely available in the Ugandan domestic pharmaceutical market (NDA registered number: NDA/MAL/HDP/3013).

The trial is designed as an open-label randomised controlled trial with four arms:

Intervention group 1: participants will take 400mg of single-dose albendazole with 200 grams of avocado.

Intervention group 2: participants will take dual-dose albendazole without taking avocado. (Participants will take 400mg of single dose albendazole for two consecutive days)

Intervention group 3: participants will take dual-dose albendazole with 200 grams of avocado. (Participants will take 400mg of single dose albendazole with 200 grams of avocado for two consecutive days)

Control group: participants will take 400mg of single-dose albendazole without taking avocado.

For participants in intervention groups 2 and 3, who are taking 400mg of albendazole on two consecutive days, they will be asked to return to the same clinic to do so.

If adverse events occur, the participants who have adverse events will be treated accordingly by the health workers who monitor the participants. If serious adverse events (SAEs) develop, these cases will be reported to VCD after recording the case(s) in the designated form, while managing the SAEs accordingly.

Three weeks after the treatment, the stool collection process will be repeated for those who participate in the treatment. These stool samples will be used to assess cure rate and egg reduction rate following albendazole treatment. If the MANE team find positive hookworm cases on the day 21 of follow up, the MANE team provide him/her alendazole again.

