The cure rate of anthelminthic drugs against STH decreases when faecal egg count is high at pre-treatment (22). But, it is also known that the fecundity of residual female hookworm increases after treatment, caused by the relaxation of adult hookworm density(23,24). It means that the faecal egg count reduction test (FECRT) can reveal a wide range of drug efficacy against STHs within different human STHs cases. Kotze and Kopp suggested exclusion of cases with the heaviest infections from a FECRT to improve the interpretation of FECRT as an indicator of drug efficacy(24).

- - - 1. **Lack of absorbing albendazole and increasing albendazole absorption with fatty meal**

When it comes to albendazole absorption in the intestine, research has shown that albendazole absorption increases five to six-fold if taken with a fatty meal (25,26). Ceballo *et al*. assessed the serum pharmacokinetics of albendazole and its metabolites in eight Argentine adults. They showed a high variation of serum concentration of albendazole sulphoxide (ABZSX) among participants, which can be one reason why people show different cure rates when taking the same dose of albendazole (27). Therefore, it is necessary to consider and evaluate approaches for increasing albendazole absorption in order to improve drug efficacy against human hookworm, since individuals have different albendazole absorption.

In previous studies done in a range of countries; Brazil, Cameroon, Cambodia, China, Ethiopia, India, Lao PDR, Tanzania, and Vietnam, the cure rate of single-dose albendazole for hookworm ranged from 36 to 93%(22,28–30). According to the study done in Gabon by Adegnika *et al*., the cure rate of double-dose albendazole for hookworm was 92%; on the other hands, the cure rate of single-dose albendazole was 54% (31).

Avocado is one of the easily accessible foods containing high fat in rural areas of Uganda. 100 g of avocado contains 15g of fat, 2g of protein, and 8.5g of carbohydrate (32).

- - - 1. **Albendazole dissolution**

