When analysing the results of the trial of fatty meal co-administration with single-, and dual-dose albendazole, the primary outcomes will be cure rate and egg reduction rate among four different groups, Chi-square (χ2) test will be applied for analysing the difference of cure rate among four treatment groups. Differences in eggs count between enrolment and follow-up will be assessed by using paired t-test. Chi-square (χ2) test or Fisher’s exact test will be applied to assess categorical variables on the difference of cure rate with four different options of treatment against hookworm. χ2 Test for trend will be used to evaluate ordered categorical variables on the difference of cure rate with four different treatment options against hookworm.

- - **Precautionary measures for the prevalence survey in the context of COVID-19**.

The WHO published the interim guideline of conducting a variety of NTDs related activities in the context of COVID-19 in the name of considerations for implementing mass treatment, active case finding and population-based surveys for neglected tropical diseases in the context of COVID-19 pandemic: interim guidance(43). According to this guideline, for conducting prevalence survey safely during the COVID-19 pandemic situation, there must be following precautionary measures as indicated in the WHO guideline. There are considerations how to take precautionary measures applicable to designated sites for planned activities (table 3 in the interim guidance), precautionary measures for health staff and community health workers (table 4 in the interim guidance), and precautionary measures for the target population(table 5 in the interim guidance).

1. Dissemination Plan

This survey will be conducted with multiple stakeholders including the ministry of health of Uganda, donor organisation (KOICA), scientists from academic partners (London School of Hygiene and Tropical Medicine), policymakers, and health professionals. The results will be written and made academic transcripts for dragging attention to reducing the NTDs burden in Uganda. The results will not reflect any personal information.

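### The cure-rate test ignores both the stratification factor and the baseline egg count; the cost is efficiency, not validity, and is smaller than the loss from testing four groups instead of the two powered margins

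*Protocol*

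**What the plan says.** - **Allocation (section 3.4).** Children are randomised by "applying the block randomisation method, stratified by health facility". There are four facilities, each with its own list, and blocks of 8 hold two places per arm.
- **Baseline egg count (Introduction, paragraph on infection intensity).** "The cure rate of anthelminthic drugs against STH decreases when faecal egg count is high at pre-treatment". No coefficient is given. Figure 1 places the egg counts of hookworm-positive samples before the arms, so every trial child has one.
- **Cure-rate analysis (section 3.7.1).** A chi-square "test will be applied for analysing the difference of cure rate among four treatment groups". The other tests listed for trial cure rate (chi-square or Fisher, and trend) take one variable at a time. The paired t-test concerns change in egg count from enrolment to follow-up. The only multivariable model in the section is for prevalence of infection in the survey.
- **Sample size (section 3.6.1, phase II).** "we power our trial to detect a difference in cure rate of 70% versus 50% for both co-administration with fatty foods versus no co-administration", and likewise for dual versus single dose. "With type I error probability of 5%, 93 participants in each comparison group will be required for 80% power". "Therefore, the total target sample size for the trial will be 186", which becomes 196 after "allowing for 5% loss to follow-up".

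**The concern.** The protocol builds facility into the randomisation and itself names a baseline measure related to cure, yet the between-arm test that it fixes uses neither.

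Stratified allocation balances the arms on facility. A test that ignores this keeps facility variation in its standard error, which is then somewhat too large if cure differs between facilities. Leaving out a baseline predictor costs power and leaves any chance difference in infection intensity uncorrected.

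Both variables are already recorded, so using them costs no data. Recruitment has little slack on the protocol's own figures: 1,650 × 12% = 198 expected positives against 196 wanted.

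The test named in section 3.7.1 is also not the comparison that section 3.6.1 powers. The gain from adjustment therefore has to be measured against the right starting point.

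**Working it through.** **1. Reproduce the plan's figure.** Inputs from section 3.6.1: 70% v 50%, alpha 5% (taken as two-sided), power 80%. With pooled variance under the null:

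n = [1.960·√(2·0.6·0.4) + 0.8416·√(0.7·0.3 + 0.5·0.5)]² / 0.20² = (1.3579 + 0.5708)² / 0.04 = 93.0

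This is 93 per group and 186 in total; 186/0.95 = 195.8, so 196. All three match. One-sided alpha would give 74 per group. The sample size is therefore that of an unadjusted one-degree-of-freedom test on each factorial margin.

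**2. Power of the test actually named.** With 186/4 = 46.5 per arm and one active factor, the arms are 50, 50, 70 and 70%, with mean 60%:

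λ = 46.5 × 4 × 0.10² / (0.6 × 0.4) = 1.86 / 0.24 = 7.75

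Non-central chi-square power is 63.9% on 3 df and 79.5% on 1 df. If both factors work additively (40, 60, 60, 80%), λ = 46.5 × 2 × 0.20² / 0.24 = 15.5 and the 3-df power is 92.6%, but rejection does not say which factor works.

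**3. Gain from adjustment, measured from the margin test.** The documents give no effect of facility or egg count on cure, so **both are assumptions**. Simulations used N = 186, marginal cure of 50% v 70% and 3,000 trials per setting. The Monte Carlo standard error is about √(0.8·0.2/3000) = 0.7 points.

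Facility SD 0.3 on the logit scale:

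| OR of cure per SD of log epg | Unadjusted margin | Facility + log epg | Gain (points) |
|---|---|---|---|
| 0.7 | 81.2% | 82.0% | 0.8 |
| 0.5 | 79.8% | 83.7% | 3.9 |
| 0.35 | 80.7% | 87.5% | 6.8 |

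Facility alone at SD 0.3, in separate runs of 2,500: 80.4 to 81.2%, 80.4 to 81.0% and 79.9 to 80.7%. That is under 1 point each time.

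A wider grid, with blocks of 8 within four equal facilities and the odds ratio expressed for non-cure:

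| Facility SD | OR of non-cure per SD | Unadjusted margin | + facility | + facility and log epg |
|---|---|---|---|---|
| 0 | 1 | 79.1% | 79.9% | 80.0% |
| 0.25 | 1.5 | 80.6% | 81.5% | 83.1% |
| 0.5 | 2 | 80.0% | 82.4% | 85.4% |
| 0.75 | 2 | 80.9% | 84.4% | 87.0% |
| 0.5 | 3 | 80.0% | 81.8% | 89.0% |

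**4. Conservatism from ignoring the stratifier.** At 50% cure, facility SD 0.3 explains about (0.25 × 0.3)²/0.25 = 2.25% of the outcome variance. The unadjusted type I error is then about 2 × [1 − Φ(1.960/√0.9775)] = 4.7%, close to nominal. Simulation gives 3.4% at facility SD 0.5 with egg-count OR 2 (4.4% adjusted for both), and 2.4% at facility SD 1 (5.5% adjusted for facility).

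**5. Splitting the gain over the written plan, one factor active.** Moving from four groups to the margin takes power from about 64% to about 80%, or 16 points. Adjustment adds roughly a further 1 to 7 points in the first table.

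**The case against.** The strongest reply is that nothing here is an error. An unadjusted comparison in a randomised trial is valid, ignoring a stratifier errs on the safe side, and the sample size holds without adjustment. All of that stands.

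The size is also open to challenge. At facility SD 0.3, facility contributes almost nothing. At an egg-count odds ratio of 0.7 the whole gain is about one Monte Carlo standard error. The larger gains need a strong egg-count effect, for which the protocol gives only a direction. That stands too, so the figures are a range under assumptions.

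It may be said that recruitment is not tight, because section 3.6.1 allows further recruitment from high-prevalence schools. That is fair: a shortfall has a remedy, and the case for adjustment does not depend on one.

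Finally, covariates are often left to a statistical analysis plan, which may exist unseen. This carries less weight, because the protocol itself names the test. The paired t-test is no answer either: it uses the enrolment count within children, for egg counts, and does not adjust the comparison of cure between arms.

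**Conclusion.** The point holds as a matter of efficiency. The named cure-rate test uses neither the facility strata nor the baseline count, although both are in hand.

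Against a margin test at about 80% power, adjustment is worth about 1 to 7 points at facility SD 0.3, nearly all of it from the assumed egg-count effect. Over the wider grid it is worth about 1 to 9 points. With no prognostic effect there is no real gain. Most of the improvement over the written plan, about 16 points when one factor works, comes from testing the margins that the sample size assumes.

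Three stronger readings are tempting and are not supported:

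- **That the unadjusted result would be biased or its error rate inflated.** It would not. Randomisation covers chance imbalance, and the error rate is at or below 5%.
- **That the sample size is wrong.** It reproduces exactly.
- **That baseline count is shown to be a strong predictor here, or that facilities are known to differ.** The protocol states a direction for the first and nothing on the second.

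**What to change.** In section 3.7.1, replace the four-group chi-square as the primary cure-rate analysis with a logistic model containing dose (dual v single), avocado (yes v no), health facility (four levels) and log baseline eggs per gram. Report for each factor the standardised (marginal) difference in cure rate with a 95% CI. This matters because the covariate-adjusted odds ratio is conditional: in the setting with facility SD 0.5 and egg-count OR 2, an unadjusted odds ratio of 2.33 (70% v 50%) corresponds to a conditional 2.66. Keep the unadjusted comparison of each margin as a sensitivity analysis.

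Log baseline count is defined for every trial child, because entry requires a positive sample.

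The cost is a rewritten paragraph rather than an added phrase, since the present plan has no dose and avocado terms to extend. No new data or visits are needed. One safeguard is worth writing in. At the design rates about 186 × 0.4 = 74 children are not cured, ample for six coefficients. If cure were near the top of the protocol's quoted 36–93% range, only about 186 × 0.07 = 13 would be. A fallback such as penalised likelihood should be named in advance.
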